#### Secondary outcomes

##### Protocol compliance

We will use a Fisher’s exact test to compare sham and rTMS proportions of participants that are compliant (complete all 20 sessions within the time frame) vs. non-compliant (fail to complete all sessions within the time frame).

##### Blinding success

We will present summary descriptive statistics, frequency (*n*) and percentages per guess category, and median certainty scores (VAS), cross-tabulated by intervention group, at each time point.

##### MRI

Proportion of participants with new lesions or enlarging lesions at the post-intervention time point will be compared between sham and rTMS using a Fisher’s exact test. Continuous MRI measures will be analysed with full factorial mixed MANOVA [within-subjects factor: time (baseline, post-treatment); between-subject factor: intervention group (rTMS, sham)], examining main effects and time*treatment interaction. If assumptions of MANOVA are violated when analysing combined MRI measures (e.g. items too highly correlated; Box’s test violated), we will split up the analyses into variable sets by tissue type and region (e.g. whole brain, lobe-specific measures separated). We may use deidentified data from publicly available MRI databases, including healthy control participants, in preliminary analyses to inform variable sets in multivariate analyses and to aid interpretation of results.

We will follow up MANOVA(s) with canonical discriminant analysis to examine rTMS/sham group separation on the linear combination of measures of myelin. We will also run univariate mixed-ANOVAs on measures of total myelin content, to examine the simple effects of intervention group at the post-intervention time point, as detailed a priori in the statistical analyses plan. False positives from multiple comparisons will be controlled using the false discovery rate (FDR) procedure [53] with threshold set at the conventional 5% level.

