#### Secondary outcomes

*Protocol compliance and adherence* to treatment schedule between active rTMS and sham control groups, comparing proportion of protocol-compliant and non-protocol compliant participants overall and separated by intervention group.*Blinding success* will be measured by asking participants which intervention they believe they received (real, placebo or unsure) immediately after the first intervention, after their 10th session, and after the final intervention. A visual analogue scale (VAS) will also be used to measure how certain participants feel about their selection of intervention group. Number and percentage of participants’ selections will be presented in a table, separated by intervention group.*MRI* data will be evaluated from scans collected at baseline (up to 2 weeks prior to the first intervention visit) and post-intervention (within 2 weeks of the last intervention visit). We will compare the mean or median, as appropriate for distribution, for rTMS and sham groups at each time point, and the change between baseline MRI and post-intervention MRI metrics of sham and rTMS intervention groups, including metrics for whole brain, lobe-specific and lesion locations.Lesion analysis: number of new and number of enlarging T2 hyperintense lesions, combined volume of lesion(s) within each lobe.Atrophy analysis: normalised percentage brain volume change from baseline to post-intervention MRI timepoints will be estimated using SIENA [26], part of FSL [27]. For substructures, including white matter, grey matter, peripheral (cortical) grey matter and ventricular cerebrospinal fluid, SIENAX [26], part of FSL-FIRST [27] will be used to determine normalised tissue volumes at each timepoint.Diffusion tensor imaging (DTI) metrics: mean diffusivity, fractional anisotropy, axial diffusivity and radial diffusivity. Considered together, these metrics are indicative of axonal and myelin integrity.Magnetization transfer ratio (MTR) and quantitative T1 mapping (qT1, mean relaxation time) will be used to measure relatively subtle changes in myelin content [28].

DTI, MTR and qT1 metrics will be obtained for tissue types combined, and for each tissue type segmented into: white matter, grey matter, peripheral (cortical) grey matter and T2 lesional tissue.

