### Sample size {14}

Thirty participants in total will be recruited. The sample size of 30 participants has been selected based on the safety and exploratory nature of the study.

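### The combined MRI MANOVA is singular as written, and the tissue-and-region fallback never removes the exact dependence among mean, axial and radial diffusivity

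*Protocol article*

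**What the plan says.** Under Statistical methods, Secondary outcomes, MRI, the protocol article states: "Continuous MRI measures will be analysed with full factorial mixed MANOVA". Time (two levels) is the within-subject factor and group (two levels) the between-subject factor.

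The measures are listed under Outcomes {12}, Secondary outcomes. The diffusion metrics are "mean diffusivity, fractional anisotropy, axial diffusivity and radial diffusivity", and MTR and qT1 are added to them. The section continues: "DTI, MTR and qT1 metrics will be obtained for tissue types combined, and for each tissue type segmented into: white matter, grey matter", and then names cortical grey matter and T2 lesional tissue. The MRI comparison is described as "including metrics for whole brain, lobe-specific and lesion locations".

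If MANOVA assumptions fail for the combined measures, the plan is: "we will split up the analyses into variable sets by tissue type and region". The examples of failure are items that are too highly correlated and a violated Box's test. The example of a split is whole-brain measures apart from lobe-specific ones. Then: "We will follow up MANOVA(s) with canonical discriminant analysis to examine rTMS/sham group separation". Univariate mixed ANOVAs on total myelin content, with a 5% false discovery rate, are also planned.

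On numbers, Sample size {14} says: "Thirty participants in total will be recruited". Trial status reports that recruitment closed at 20. Section {20c} removes anyone with only one MRI time point from all MRI analyses, and section {18b} excludes non-compliant participants from the follow-up scan. The MRI sample is therefore at most 20.

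**The concern.** A MANOVA needs an error matrix that can be inverted. That requires variables that are not exact combinations of one another, and fewer of them than there are error degrees of freedom to support them. The combined set appears to fail both conditions. The protocol foresees excessive correlation, but its remedy divides the variables along an axis (tissue and region) that leaves the redundant metrics together.

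If this stands, the multivariate MRI analysis cannot be run as described. What is reported would then depend on how the software treats a singular matrix, or on a choice of variables made after the data are seen. The discriminant follow-up adds a second risk: with this few participants, a fitted linear combination separates two groups well even when nothing differs between them.

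**Working it through.** The protocol states no power or dimension calculation to reproduce, so the check is one of rank.

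**Inputs**
- Metrics per tissue and region: MD, FA, AD, RD, MTR, qT1 = 6 (Outcomes {12}).
- Tissue classes: combined, white matter, grey matter, cortical grey matter, T2 lesional tissue = 5 (same section).
- Lobes: number not stated; 4 assumed, range 4 to 6.
- Participants: 30 planned (Sample size {14}), 20 recruited (Trial status). A 13:7 split at 20 is assumed from the 2:1 ratio in section {16a}.
- Definitions: the protocol names the diffusion metrics without formulas. The standard ones are used, with tensor eigenvalues λ1 ≥ λ2 ≥ λ3: AD = λ1, RD = (λ2 + λ3)/2, MD = (λ1 + λ2 + λ3)/3.

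**Step 1, linear dependence.** From these definitions MD = (AD + 2 × RD)/3 in every voxel. Averaging is linear, so the identity carries over to regional means over the same voxels. Numerically the largest voxel discrepancy was about 2e-16, and the discrepancy for a regional mean was 0. For regional medians it was about -0.003 on simulated eigenvalues, so medians give near-singularity rather than exact singularity.

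**Step 2, variable count.** Whole brain: 6 × 5 = 30. With lobes: 30 × (1 + 4) = 150 up to 30 × (1 + 6) = 210. Volumes come on top.

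**Step 3, error degrees of freedom.** With two groups, N - 2 = 28 at N = 30 and 18 at N = 20. With two time points, the time-by-group test is a Hotelling T² on change scores. The rank of its error matrix is at most the smaller of N - 2 and the number of linearly independent variables.

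**Step 4, rank of the error matrix on simulated data**

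| Variable set | Variables | Rank, N = 30 | Rank, N = 20 |
|---|---|---|---|
| Whole brain, five tissues | 30 | 25 | 18 |
| One tissue, four lobes | 24 | 20 | 18 |
| One tissue, one region | 6 | 5 | 5 |
| Whole brain, five tissues, MD dropped | 25 | 25 | 18 |
| One tissue, four lobes, MD dropped | 20 | 20 | 18 |
| One tissue, one region, MD dropped | 5 | 5 | 5 |

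All three sets that keep MD are singular at both sample sizes. Splitting to one tissue in one region brings 6 variables under 18 and 28, which settles the degrees-of-freedom problem but leaves rank 5 of 6. Following the protocol's own example, with whole-brain measures apart from lobe-specific ones and tissues kept together, 30 variables remain.

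**Step 5, the named trigger.** Box's test uses the log determinant of each arm's covariance matrix. With MD, AD and RD all present, that determinant is zero in both arms, so the test is undefined.

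**Step 6, what software does.** At N = 20 one generalized-inverse routine (statsmodels) gave F on 5 and 14 degrees of freedom for the 6-variable set. It gave 0 denominator degrees of freedom and no p-value for the 30-variable set.

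**Step 7, after the correction.** With MD dropped and one tissue in one region, the F degrees of freedom are p and N - 1 - p: 5 and 20 - 1 - 5 = 14 at N = 20; 5 and 30 - 1 - 5 = 24 at N = 30. The condition number is about 8 to 11.

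**Step 8, discriminant analysis with no effect present.** These figures come from 4,000 runs with equal priors, each participant classified by the function fitted to the same data. At 13/7, apparent accuracy was 72% with 5 variables, 75% with 6 and 91% with 12. At 20/10 it was 68%, 70% and 81%. Balanced accuracy, for which chance is 50%, was essentially the same.

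**The case against.** Several objections have force.

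- **The fallback does work for degrees of freedom.** Read literally, a split by tissue and by region gives 6 variables, well under 18. This stands. A reader might infer that the fallback cures neither problem, and the text does not support that. It leaves coarser splits open, and its example suggests one, but it does not require them.
- **The test need not crash.** A reader might infer that no MANOVA can be computed. For the 6-variable set, generalized-inverse software returns a valid five-dimensional test. Nor does it matter which diffusivity is removed, because any two of the three span the same space. In a check at 13/7, T² was 13.681 whichever was dropped. With one removed, null rejection was 4.6% at 13/7 and 4.7% at 20/10 (4,000 runs, normal data). The collinearity therefore does not bias the test.
- **The discriminant figures need context.** They rest on equal priors, and the protocol promises no classification accuracy. Labelling everyone rTMS would be right for 13/20 = 65% or 20/30 = 67%. The 12-variable figure does not correspond to a single tissue-region set. What remains is that apparent separation is inflated and no validation is mentioned.
- **Details are deferred.** A separate analysis plan is to be signed off before data lock, public MRI data may inform the variable sets, and analyses may be modified on test assumptions. That would answer a charge of missing detail. It does not answer this one: the protocol itself names the model, the metrics, the trigger and the remedy, and gives no rule for removing a redundant metric or limiting set size.

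**Conclusion.** Wrong as written. The combined MRI MANOVA has a singular error matrix for two independent reasons: the MD, AD and RD dependence at any sample size, and at least 30 variables against 28 or at most 18 error degrees of freedom. The fallback resolves the second only when each tissue-region set is analysed on its own. It never resolves the first, although excessive correlation is one of its own triggers: every tissue-region set of the six metrics keeps rank 5 of 6.

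The exact dependence assumes regional means over common voxels; with medians it is near-exact. The 13:7 split and the number of lobes are assumptions, but the conclusion for the whole-brain set and for the single tissue-region set depends on neither.

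A reader might also infer that this is the decisive test for moving to phase II. The documents do not say so. Myelin change on MRI is a secondary objective in an exploratory phase 1 framework, and the FDR-controlled univariate ANOVAs need no matrix inversion across metrics. The correction is worth making but is not critical to the trial.

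**What to change.** Before data lock, amend the MRI analysis text or settle the following in the statistical analysis plan:

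1. Keep at most two of MD, AD and RD in any multivariate set.
2. Replace the all-variable MANOVA with tissue-by-region sets named in advance, each with far fewer variables than N - 2. About five variables gives F on 5 and 14 degrees of freedom at N = 20.
3. If the canonical discriminant analysis is kept, report group separation only with leave-one-out or permutation assessment.

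The cost is a few lines of wording and the loss of a single omnibus test over all metrics. No data collection changes, and Trial status reports that no intervention comparison had been analysed at submission. Deleting the discriminant analysis, or replacing the MANOVA with a short univariate list, would also work but is a matter of preference.

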##### Participant-reported questionnaire and Floodlight data

Continuous outcomes (AQol8D, HADS, FSS, U-Turn speed and Draw a Shape tracing error) will be compared between rTMS and sham conditions with univariate mixed-ANOVAs, as described above for MRI. Significant time by intervention interactions will be followed up with simple effects tests, comparing rTMS to sham group means within each time point.

Outcomes with count data (e-SDMT, Pinching, tracing error in the Draw a Shape test) will be analysed using Mann-Whitney *U* test to compare medians between rTMS and sham groups within each time point. The time by intervention interaction will also be examined using Mann-Whitney *U* tests on within-subject change from baseline, separately for the post-intervention and follow-up timepoints, controlling for false positives using FDR set at 5% threshold.

The statistical analyses carried out may be modified based on distributions observed and test assumptions. For all statistics, the level for significance will be set at *p*<0.05. Summary statistics will be prepared with means and standard deviations considered for normally distributed outcomes or median and interquartile range for non-normally distributed outcomes, as appropriate.

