## Assignment of interventions: allocation

### Sequence generation {16a}

After confirming study eligibility, participant allocation to rTMS or sham will be performed automatically using REDCap software. We will use an allocation ratio of 2:1, with twice as many participants allocated to the active rTMS group as sham control, stratified by sex and a block size of 6.

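### Draw a Shape tracing error is assigned to two different tests, and the within-time-point arm contrasts for secondary outcomes are not adjusted for baseline or for the sex stratifier

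*Protocol article*

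**What the plan says.** All places are in the protocol article.

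- **Draw a Shape.** Under Participant-reported questionnaire and Floodlight data, the mixed-ANOVA list reads "Continuous outcomes (AQol8D, HADS, FSS, U-Turn speed and Draw a Shape tracing error". The next paragraph, on Mann-Whitney tests, opens "Outcomes with count data (e-SDMT, Pinching, tracing error in the Draw a Shape test". Secondary outcomes defines the measure as a Hausdorff distance averaged over the shapes.
- **Continuous questionnaire and app outcomes.** These "will be compared between rTMS and sham conditions with univariate mixed-ANOVAs, as described above for MRI". The MRI model has "within-subjects factor: time (baseline, post-treatment); between-subject factor: intervention group (rTMS, sham" as its factors. Then: "Significant time by intervention interactions will be followed up with simple effects tests, comparing rTMS to sham group means within each time point".
- **Count outcomes.** Mann-Whitney tests are used "to compare medians between rTMS and sham groups within each time point". A second set of Mann-Whitney tests uses each person's change from baseline, with 5% FDR control.
- **MRI.** After the MANOVA, univariate mixed ANOVAs on total myelin content are run "to examine the simple effects of intervention group at the post-intervention time point".
- **Allocation.** Sequence generation {16a}: 2:1, "stratified by sex and a block size of 6". Sex is in none of the models described.

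**The concern.** There are two separate problems.

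The first is a contradiction. A tracing distance is not a count, and listing it under both headings gives one outcome two analyses. The same section lets the analyses be modified once distributions are seen, so the choice between the two could be made after the data are known.

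The second is how the arms are compared at a given time. The questionnaires and app tests have three time points, so their time-by-group interaction is an omnibus test. The only arm contrast named at the end of treatment or at 4 months is then the difference in raw means. That contrast carries all of the chance baseline difference between two small groups. A genuine interaction could be followed by an unremarkable raw contrast, or by one that mostly reflects imbalance at entry. In the questionnaire and app section, comparing arms within each time point also includes baseline, where randomisation means there is no treatment effect to find. These results are meant to inform a phase II trial.

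**Working it through.** **Draw a Shape.** The two lists name the same quantity. The definition in Secondary outcomes, and the Draw a Shape section's use of Hausdorff distance, make it continuous. The mixed-ANOVA entry fits that definition and the count entry does not.

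**Inputs for the variance comparison.** The plan states no variance, effect size or power, so there is no figure of its own to reproduce. The only usable inputs are the retest ICCs in the instrument sections. Assume that the baseline-post correlation r equals the ICC and that variances are equal at both times. Per unit of outcome variance:

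- post-only contrast: 1
- change from baseline: 2(1 - r)
- ANCOVA on baseline: 1 - r²

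So post-only/ANCOVA = 1/(1 - r²), and change/ANCOVA = 2/(1 + r).

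| Outcome | ICC = r | Post-only/ANCOVA | Change/ANCOVA |
|---|---|---|---|
| AQoL-8D | 0.70 | 1/(1 - 0.4900) = 1.96 | 1.18 |
| Pinching | 0.72 | 1/(1 - 0.5184) = 2.08 | 1.16 |
| FSS | 0.76 | 1/(1 - 0.5776) = 2.37 | 1.14 |
| HADS, U-turn | 0.83 | 1/(1 - 0.6889) = 3.21 | 1.09 |
| e-SDMT, Draw a Shape | 0.85 | 1/(1 - 0.7225) = 3.60 | 1.08 |

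With two time points, the mixed-ANOVA interaction is a comparison of change, so the last column applies to it as well as to the change-from-baseline tests.

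**Lower correlations.** Post-only/ANCOVA falls to 1.56 at r = 0.6, 1.33 at r = 0.5 and 1.10 at r = 0.3. Change/ANCOVA moves the other way: 1.25, 1.33 and 1.54.

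**Small samples.** The formulas ignore the cost of estimating the covariate slope. In simulation (20,000 runs per setting), post-only/ANCOVA was 1.89 (r = 0.70) and 3.47 (r = 0.85) with 20:10. It was 1.84 and 3.43 with 13:7. Change/ANCOVA was 1.13 and 1.04 with 20:10, and 1.11 and 1.02 with 13:7. The 13:7 split is assumed; Trial status says only that recruitment closed at 20.

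**Chance imbalance at 13:7.** The standard error of the baseline difference is √(1/13 + 1/7) = √0.220 = 0.47 SD.

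**Illustrative power.** Assumed 1 SD effect, 13:7, r = 0.70, two-sided 5%, normal approximation: post-only 57%, change 79%, ANCOVA 85%.

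**What cannot be calculated.** No retest ICC is given for any MRI metric, and nothing says how much outcome variance sex explains.

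**The case against.** A reader might infer that the plan ignores baseline altogether and that all its group comparisons lose two- to nearly fourfold in variance. The text does not support that. In the mixed models baseline is a level of time, and the interaction uses it. The count outcomes have a change-from-baseline test beside the raw one. For the continuous questionnaire and app outcomes, raw means are compared only after a significant interaction, so a test that already uses baseline decides whether an effect is declared. The raw contrasts not tied to an interaction are the within-time-point Mann-Whitney tests and, as worded, the MRI simple effect. All this stands and limits the size of the point.

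Retest ICCs describe stability without treatment, mostly over unstated intervals. The correlation over 4 weeks to 4 months may be lower, so the range is nearer an upper bound. This also stands.

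It would be tempting to add that the two Draw a Shape tests fall under different multiplicity rules. That is not established, because the mixed ANOVAs are to follow the MRI description, which includes FDR control.

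Covariates are often left to the statistical analysis plan, to be signed before data lock. The absence of sex from an article's model description is therefore not a demonstrated error; including it is a recommendation. The deferral does not remove the raw contrasts or the double listing, which the article states outright.

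Finally, Protocol strengths and limitations says the sample is too small to study effects that differ by baseline. That concerns effect modification and is no reason to omit a single baseline covariate.

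**Conclusion.** The double assignment of Draw a Shape tracing error is a plain contradiction and needs no assumption.

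The adjustment point holds for three sets of contrasts: the MRI simple effects after treatment, the simple effects that follow a significant interaction, and the within-time-point Mann-Whitney tests. For the questionnaire and app contrasts only, the unadjusted variance is about 2.0 to 3.6 times that of ANCOVA, assuming equal variances and r equal to the quoted ICCs (0.70-0.85); at r = 0.5 it is 1.33 times. The interaction and change tests lose only about 8-18% over the same ICC range. The larger range cannot be carried over to MRI, and none of it is due to sex. These are secondary outcomes of a phase 1 trial, and the primary adverse-event comparison is untouched.

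**What to change.** 1. Remove Draw a Shape tracing error from the count list and analyse it once, as continuous.
2. For each continuous or count secondary outcome, report one rTMS-sham difference with a 95% CI at post-intervention, and also at 4 months for questionnaires and app tests. Take it from an ANCOVA or mixed model with that outcome's baseline value and sex as covariates, on ranks if skewed.
3. Let these estimates replace the raw within-time-point contrasts, and drop the group tests at baseline.

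The cost is wording, since baseline values and sex are already collected, plus about 2 degrees of freedom. With 20 participants the error degrees of freedom go from 18 to 16 and the two-sided 5% critical t from 2.101 to 2.120 (2.120/2.101 = 1.009, about 1%). The article reports that no intervention comparison had been analysed at submission, so the change can be written into the statistical analysis plan before data lock.
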